## Materials and Methods

### Inclusion/Exclusion Criteria

The intervention program will be offered to mothers who had recently experienced a perinatal death, including: having lost a child during pregnancy because of miscarriage (i.e., embryo or fetus death prior the 28th week of gestation); termination due to medical indications; stillbirth (i.e., fetus death after 28 completed weeks of gestation); or neonatal death (i.e., infant death within the first 7 days of life). Women who have experienced perinatal death while pregnant within no more than 1 year before the enrollment will be invited to participate to the study. Exclusion criteria include significant vision impairments despite wearing corrective glasses or lenses, presence of a diagnosed mental disorder, and being under psychological treatment. The target sample will be composed of 40 women. To evaluate the size of the involved samples, we used a Sample Size Calculation (Power Analysis) using the software GPower^∗^3. We based the power-analysis on a recent study assessing efficacy of an EMMA’s World-based intervention for the treatment of stress-related disorders. We estimated a minimum of 40 women to be included in the trial, in order to achieve a minimum power of 90%, considering a medium effect size of *f* = 0.25, and a significance level of 0.05.

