
#### Satisfaction With the Intervention

Women’s satisfaction with the intervention will be rated at post-test using the Client Satisfaction Questionnaire (CSQ-8; Attkisson and Zwick, 1982). The CSQ-8 is a self-report measure designed to assess clients’ satisfaction with mental health services. The 8-items versions has eight question-items (quality of service, kind of service, met needs, recommend to a friend, amount of help, deal with problems, overall satisfaction, and come back), rated using a 4-point Likert scale, with a possible total scores can vary from 8 to 32. Higher scores indicate greater satisfaction with the service.

In order to test our hypothesis, we will perform repeated measures (Mixed Model) ANOVA with 3 Times (Pre, Post-test 1, Post-test 2) and 2 Conditions (VR-based intervention first, followed by TAU, i.e., VR+TAU; TAU first, followed by VR-based intervention, i.e., TAU+VR). For ethical reasons, the study is a randomized control crossover design, where all participants receive an intervention. The Pretest to Post-test 1 allows the comparison of VR-based treatment versus TAU, and the Post-test 1 to Post-test 2 allows to test the added value of the VR-Based intervention to TAU.

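### The 90% power for a medium effect with 40 women fits a repeated-measures interaction worth about 1 SD between arms, not a medium VR-versus-TAU difference

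*Protocol article*

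**What the plan says.** All quotes are from the protocol article.

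- **Size and power** (Inclusion/Exclusion Criteria): "The target sample will be composed of 40 women". The basis is that "we used a Sample Size Calculation (Power Analysis) using the software GPower", with the inputs "considering a medium effect size of *f* = 0.25" and "and a significance level of 0.05". The result: "We estimated a minimum of 40 women to be included in the trial, in order to achieve a minimum power of 90" per cent. The text does not say which test or contrast the f belongs to.
- **Analysis** (end of the section Satisfaction With the Intervention): a "repeated measures (Mixed Model) ANOVA with 3 Times (Pre, Post-test 1, Post-test 2) and 2 Conditions", the conditions being the two treatment orders.
- **Contrast for hypothesis (a)** (same place): "The Pretest to Post-test 1 allows the comparison of VR-based treatment versus TAU".
- **Hypotheses** (end of the Introduction): (a) VR given first reduces symptoms more than TAU does; (b) women who receive VR after TAU improve from before to after VR. Hypothesis (b) concerns one sequence only.

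**The concern.** The hypotheses are two narrow contrasts: about 20 women against 20 over the first period, and a change within about 20 women over the second. The power statement names neither. It attaches 90% to an effect called medium, which most readers will take as a difference of about half a standard deviation between VR and TAU. In G*Power's repeated-measures routine the same f = 0.25 stands for a much larger gap between the arms.

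At stake is how the trial is judged, before and after it runs. Anyone who takes the statement at face value will believe that a moderate advantage of VR would very probably be detected.

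**Working it through.** **Inputs from the article:** N = 40, f = 0.25, alpha 0.05, power at least 90%, 2 conditions, 3 times.

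**Assumptions, since the article does not give them:** 1:1 allocation (20 per arm), two-sided tests, sphericity, no dropout, and a common correlation r between measurements, shown over a range (0.5 is G*Power's default).

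**Step 1. Reproduce the stated figure.** For the interaction, with m times and 2 groups, the noncentrality is λ = f² × N × m / (1 − r), with degrees of freedom (m − 1) and (N − 2)(m − 1). For m = 3, N = 40 the numerator is 0.0625 × 40 × 3 = 7.5, with df 2 and 76.

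| r | λ | Power |
|---|---|---|
| 0.3 | 10.71 | 83% |
| 0.45 | 13.64 | 91.0% |
| 0.5 | 15.00 | 93.5% |

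At r = 0.5, N = 36 already gives 90.6%. So 40 women and at least 90% are consistent with the planned analysis.

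The Pre/Post-test 1 interaction alone (m = 2, numerator 5.0, df 1 and 38) gives 86.9% at r = 0.5, 90.1% at 0.55 and 93.1% at 0.6. It too can yield the stated figure, so the article's numbers do not identify which routine was used.

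**Step 2. Translate f = 0.25 into a gap between arms.**

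- *2 x 3, gap of d SD at Post-test 1 only.* Each arm lies d/2 from the common mean at that time. After centring over the three times, the interaction effects are −d/6, d/3, −d/6. Their mean square is (d²/36 + d²/9 + d²/36)/3 = d²/18. Hence d = 0.25 × √18 = 1.06 SD.
- *2 x 2, Pre and Post-test 1.* The effects are ±d/4, so f = d/4 and d = 1.0 SD.

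By contrast, f = 0.25 for a plain two-group comparison is d = 2f = 0.5 SD. Hence 0.5 SD is used below as the medium group difference.

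**Step 3. Power for 0.5 SD at Post-test 1 (hypothesis (a), 20 per arm).**

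- Planned 2 x 3 interaction: f² = 0.25/18 = 0.0139, so λ = 0.0139 × 120/(1 − r) = 3.33, 5.56 and 8.33 at r = 0.5, 0.7 and 0.8.
- Change score: standardised difference 0.5/√(2(1 − r)) = 0.50, 0.65, 0.79, multiplied by √10 for the noncentral t on 38 df.
- ANCOVA, shown for comparison because it is not the stated analysis: 0.5/√(1 − r²) = 0.58, 0.70, 0.83.

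| Analysis | r = 0.5 | r = 0.7 | r = 0.8 |
|---|---|---|---|
| Planned 2 x 3 interaction | 34% | 53% | 72% |
| Change score | 34% | 51% | 68% |
| ANCOVA (not planned) | 43% | 58% | 73% |

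A comparison of Post-test 1 scores alone gives 34% whatever the correlation.

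**Step 4. Hypothesis (b), about 20 women, paired.** The standardised change is 0.5/√(2(1 − r)), multiplied by √20, on 19 df. Power for a 0.5 SD change is 56% at r = 0.5, 78% at 0.7 and 92% at 0.8.

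**Step 5. Difference detectable with 90% power, 20 per arm.** On post scores it is 1.05 SD. For change scores multiply by √(2(1 − r)): 1.05 at r = 0.5 and 1.05 × 0.775 = 0.81 at r = 0.7. With baseline adjustment multiply by √(1 − r²): 0.91 at r = 0.5 and 0.75 at r = 0.7.

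**The case against.** The strongest reply is that nothing was miscalculated. The planned analysis is the 3 x 2 mixed ANOVA, f = 0.25 is the customary medium value, and at the default correlation 40 women exceed 90%. The article never mentions a standardised difference of 0.5, so computing power for it brings in an input that the authors did not choose. Repeated measurements may also correlate strongly, and the correlation is a detail that an article may leave to the full protocol.

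Much of this stands. The arithmetic is consistent, and leaving out the correlation is not in itself a fault. A reader might infer that the figure can come only from the three-time interaction; Step 1 shows that the two-time version also reaches 90.1% at r = 0.55. A reader might also infer that 90% is missed for both hypotheses in every case. The documents do not support that: if f = 0.25 is meant on the interaction scale, hypothesis (a) has 87 to 93% at r = 0.5 to 0.6, and hypothesis (b) reaches 92% for a 0.5 SD change at r = 0.8.

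What the reply does not remove is the label. On the scale where 90% holds, the effect is about 1 SD between arms. Under the article's own planned interaction, with no other test substituted, a 0.5 SD gap has 34 to 72% power over r = 0.5 to 0.8.

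**Conclusion.** The point holds as a mismatch between the power statement and the contrasts in the hypotheses; it is not a calculation error. It should be fixed, but it does not invalidate the design. At least 90% power with 40 women is right for an interaction equal to a VR-versus-TAU gap of 1.0 to 1.06 SD, given a correlation of about 0.45 or more (three times) or 0.55 or more (two times). It is not right for a medium difference between VR and TAU: none of the analyses examined reaches 90% for 0.5 SD at correlations up to 0.8, the highest figure being 73% with an ANCOVA that is not planned. For hypothesis (b) the answer turns on the correlation.

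These figures assume 20 per arm, sphericity and complete data.

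Two further inferences are tempting but not supported. The target equals the stated minimum, which might suggest that dropout was ignored; an article commonly leaves that allowance to the full protocol. The effect size might seem unsuitable because the power analysis draws on a study in stress-related disorders while this trial excludes "presence of a diagnosed mental disorder, and being under psychological treatment"; that study is not at hand, and the article does not say that f = 0.25 was its observed effect.

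**What to change.** Keep 40 women and reword the sample-size paragraph:

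1. Name the test and contrast to which f = 0.25 belongs, and the correlation assumed.
2. Replace the claim of 90% power for a medium effect with the detectable difference for hypothesis (a): with 20 per arm, about 1.05 SD at 90% power (post score, or change score at correlation 0.5). If a baseline-adjusted analysis is adopted, the figure is about 0.9 SD at correlation 0.5.
3. Give the power for a 0.5 SD difference at Post-test 1 under the planned analysis (about 34%, 53% and 72% at correlations 0.5, 0.7 and 0.8).
4. Give the power for hypothesis (b) separately, on about 20 women (56%, 78% and 92% at the same correlations).

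The cost is wording only, with no extra participants and no change of design. The drawback is that the stated figure becomes less favourable.

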### Measures and Data Analysis

#### Personal Information Sheet

Women will be asked about their age, nationality, relationship status, religion, education level, occupation, French proficiency, presence of psychiatric and/or physical problems (i.e., mobility and sight problems), being under psychological treatment and use of drugs. In addition, women will be asked to provide information about their perinatal loss: date of perinatal death, type of perinatal death (i.e., miscarriage, termination due to medical indications, voluntary termination of pregnancy, stillbirth, or neonatal death), gestation weeks, previous pregnancy, planned pregnancy, previous children.

#### Outcome Measures

Perinatal grief will be measured with the Perinatal Grief Scale (PGS; Potvin et al., 1989; Toedter et al., 2001; French validation: Paris et al., 2017). The PGS is composed by 33 statements divided into three subscales: Active Grief, which includes 11 items that refers to the normal emotional reactions to the loss (i.e., sorrow, missing the child, or crying); Difficulty Coping, which includes 11 items that refers to more complex emotional reactions (e.g., difficulty with normal life activities, lack of support, problems in marital relationships); and Despair, which refers to long-term effects of the loss (e.g., existential feelings of helplessness and hopelessness) and relevant coping strategies. The PGS uses a Likert type scale with five response options ranging from 1 (i.e., “strongly disagree”) to 5 (i.e., “strongly agree”). The total score varies between 33 and 165 points, with values above 91 points represent potential psychiatric morbidity. Complicated grief will be measured with the Inventory of Complicated Grief (IDC; Prigerson et al., 1995; French adaptation: Zech, 2006). This instrument consists of 19 items concerning the immediate bereavement-related thoughts and behaviors of the respondent, who is asked to report the frequency (from “0 = never” to “4 = always”) with which he/she currently underwent each of the emotional, cognitive, and behavioral states detailed in the instrument. Individuals with an ICG total scores > 25 reported to have significantly worse general, mental and physical health, social functioning, and bodily pain, as well as depression. Thus, the authors concluded that this score should be the criterion for distinguishing between uncomplicated and complicated grief reactions. Depressed mood will be assessed using the Beck Depression Inventory-II (BDI-II; Beck et al., 1996; Validated in French by Édition du centre de psychologie appliquée, 1996). The BDI-II is one of the most widely used instruments to assess depressive symptoms and their severity following the criteria of the Diagnostic and Statistical Manual of Mental Disorders (DSM-IV; American Psychiatric Association, 2000). The BDI-II consists in 21 symptoms assessed with multiple-choice responses rated on a scale value of 0–3. The maximum total score is 63, with the following standardized cutoffs: 0–13: associated to normal minimal range, 14–19: associated to mild depression, 20–28: associated to moderate depression, and 29–63: associated to severe depression. Postnatal depression will be assessed through the 10-item Edinburgh Postnatal Depression Scale (EDPE; Cox et al., 1987). The EPDS is the most commonly used screening tool to determine women’s clinically significant signs of depression during the perinatal period (e.g., McCabe-Beane et al., 2016). Since many symptoms of depression overlap with normal states in women during the perinatal period (e.g., sleep disturbance), EPDS items were planned to evaluate only the mood components of depressive symptoms. The 10 items are rated on a scale from 0 to 3, and are reflecting the mood during in the last 7 days. EPDS score of 10 and 13 are proposed as cut-off scores indicative of potential minor or major depression, respectively (Cox et al., 1987; see McCabe-Beane et al., 2016 for other cut-off scores). Anxiety will be assessed using the State and Trait Anxiety Inventory-form Y (STAI-Y; Spielberger, 1983; French validation: Gauthier and Bouchard, 1993). It consists of a self-report instrument conceived to evaluate trait (a stable personality trait) and state (a temporary and fluctuating condition) anxiety. The STAI-Y consists of two subscales (trait and state anxiety) with 20 items each rated on a 4-point scale. Higher scores indicate greater anxiety. Affect will be measured with the Positive and Negative Affect Scale (PANAS; Watson et al., 1988; French validation: Gaudreau et al., 2006). The PANAS is a widely used scale which consists of two subscales, one measuring positive affect and the other assessing negative affect. Each subscale is composed of 10 items, scored on a 5-point Likert scale ranging from 1 (i.e., “very slightly or not at all”) to 5 (i.e., “extremely”). Clinical global impression assessed by the therapist will be assessed at pretest and post-test using the Clinical Global Impression rated by the therapist (CGI; Guy, 1976). It consists in a 3-item observer-rated scale that measures illness severity (CGIS), global improvement or change (CGIC) and therapeutic response. The CGI is rated on a 7-point scale, with the CGIS characterized by a range of responses from 1 (i.e., “normal”) to 7 (i.e., “amongst the most severely ill patients”). CGI-C scores range from 1 (i.e., “very much improved”) to 7 (i.e., “very much worse”). Treatment response ratings should consider both treatment-related negative events and therapeutic efficacy, ranging from 0 (i.e., “marked improvement and no side-effects”) to 4 (i.e., “unchanged or worse and side-effects outweigh the therapeutic effects”). Each CGI’s component is rated separately, and this instrument does not provide a global score.

#### Satisfaction With the Intervention

Women’s satisfaction with the intervention will be rated at post-test using the Client Satisfaction Questionnaire (CSQ-8; Attkisson and Zwick, 1982). The CSQ-8 is a self-report measure designed to assess clients’ satisfaction with mental health services. The 8-items versions has eight question-items (quality of service, kind of service, met needs, recommend to a friend, amount of help, deal with problems, overall satisfaction, and come back), rated using a 4-point Likert scale, with a possible total scores can vary from 8 to 32. Higher scores indicate greater satisfaction with the service.

In order to test our hypothesis, we will perform repeated measures (Mixed Model) ANOVA with 3 Times (Pre, Post-test 1, Post-test 2) and 2 Conditions (VR-based intervention first, followed by TAU, i.e., VR+TAU; TAU first, followed by VR-based intervention, i.e., TAU+VR). For ethical reasons, the study is a randomized control crossover design, where all participants receive an intervention. The Pretest to Post-test 1 allows the comparison of VR-based treatment versus TAU, and the Post-test 1 to Post-test 2 allows to test the added value of the VR-Based intervention to TAU.

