
The objective of the proposed paper is to describe the protocol of a randomized control trial aimed to assess a VR-based intervention for mothers who are experiencing perinatal loss. We hypothesize that: (a) when administered before TAU, the VR-based intervention will lead to a greater reduction in symptoms related to grief, postnatal depression and general psychopathology, compared to participants receiving TAU; (b) when administered after TAU, the participants will show a significant pre/post-VR-based intervention improvement in symptoms related to grief, postnatal depression and general psychopathology.

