**FIGURE 3 F3:**
[figure not shown]
CONSORT flowchart for the proposed clinical trial: adapted from Consort 2010.

Women will be randomly assigned to the VR+TAU or to the TAU + VR condition. Randomization will be performed using a true random number service^2^, and will be not stratified based on participant’s characteristics. The TAU condition is a homogenous standard program proposed by the CERIF at UQO based on group counseling offered to women and men who experienced a perinatal loss. The TAU condition as well as the VR-based intervention will last 3 weeks, after which women will complete a post-assessment (see Figure 3). The VR-based intervention will be conducted at the Cyberpsychology Laboratory of UQO; the TAU group counseling will take place at the CERIF of UQO.

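### If the three-time ANOVA is a mixed-design ANOVA, as its wording suggests, missing only Post-test 2 would remove a woman from the VR-versus-TAU comparison already observed at Post-test 1

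*Protocol article*

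**What the plan says.** The analysis paragraph stands at the end of Measures and Data Analysis, under Satisfaction With the Intervention. To test the hypotheses, "we will perform repeated measures (Mixed Model) ANOVA with 3 Times (Pre, Post-test 1, Post-test 2) and 2 Conditions". The two conditions are the two treatment orders, and "the study is a randomized control crossover design, where all participants receive an intervention".

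The same paragraph gives each interval its own job. On the first interval it says: "The Pretest to Post-test 1 allows the comparison of VR-based treatment versus TAU". The second interval, after the switch of treatment, has a different purpose, since "the Post-test 1 to Post-test 2 allows to test the added value of the VR-Based intervention to TAU".

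Hypothesis (a), at the end of the Introduction, concerns the first interval: "when administered before TAU, the VR-based intervention will lead to a greater reduction in symptoms related to grief".

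Under Procedure, the timing is: "The TAU condition as well as the VR-based intervention will last 3 weeks, after which women will complete a post-assessment".

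Under Inclusion/Exclusion Criteria, the size is justified with G*Power: "We estimated a minimum of 40 women to be included in the trial, in order to achieve a minimum power of 90" per cent. The effect assumed for this is worded as "considering a medium effect size of *f* = 0.25", with alpha set at 0.05. The number of measurements, the correlation between them and the test family are not given there.

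**The concern.** The randomised comparison of VR with TAU is finished at Post-test 1, before anyone changes treatment. The stated model nevertheless spans all three assessments.

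In a mixed-design ANOVA with one between-woman factor and one three-level within-woman factor, standard software drops any woman with a missing score. A woman with Pre and Post-test 1 but no Post-test 2 would therefore disappear from the test of hypothesis (a).

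Two things are at stake. Precision falls with any second-period loss, in a trial of only 40 women. In addition, whether a woman counts in the first-period contrast would depend on what she does after it. The second treatment differs by sequence: group counselling for those who had VR first, therapist-led VR for those who had TAU first. Leaving may therefore relate to first-period response differently in the two sequences. If it does, the VR-versus-TAU estimate is biased.

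**Working it through.** **Inputs.** From the article: 40 women, f = 0.25, alpha 0.05, two conditions, three times. Assumed, because not stated: 1:1 allocation (20 per arm), SD 1 at each time, correlation ρ = 0.5, every woman has Post-test 1, second-period loss of 5% to 30%.

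**1. The plan's own figure.** For the within-between interaction in a repeated-measures F test with k = 2 groups and m times:

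- λ = f²·N·m/(1−ρ), df1 = (k−1)(m−1), df2 = (N−k)(m−1).
- With m = 3 and N = 40: λ = 0.0625 × 40 × 3/0.5 = 15, df 2 and 76, power 0.935.
- The smallest even N that reaches 90% is 36 at ρ = 0.5 and 40 at ρ = 0.45.

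So 40 women meet the stated minimum under this test, although the unstated inputs prevent a unique reproduction. The between-condition test at ρ = 0.5 would need 116. The stated size therefore fits a classical repeated-measures calculation but does not prove that one was used.

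**2. Precision of the Pre to Post-test 1 contrast.** The variance of a woman's change is 2(1−ρ) = 1.

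- All 40 women: SE = √(1/20 + 1/20) = 0.316.
- 20% lost per arm, 16 + 16 left: SE = √(1/16 + 1/16) = 0.354, about 12% larger.

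**3. Power of the same contrast.** With m = 2, λ = 0.0625 × N × 2/0.5 = 0.25N, df 1 and N−2.

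| Second-period loss | Women kept | λ | Power |
|---|---|---|---|
| none, or partial cases kept | 40 | 10 | 0.869 |
| 5% | 38 | 9.5 | 0.851 |
| 10% | 36 | 9 | 0.830 |
| 20% | 32 | 8 | 0.781 |
| 30% | 28 | 7 | 0.721 |

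In this convention f = 0.25 corresponds to a difference in change of √10 × 0.316 = 1.0 SD, so the power figures refer to a large difference in change.

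**4. Bias when only three-visit completers are kept.** Take change in symptoms, negative favouring VR, with no true effect.

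- *Random loss:* none.
- *Less improved half of the VR-first arm supplies that arm's 20% loss, TAU-first loss random:* the two halves of a standard normal have means −0.798 and +0.798. The mean of those left is (0.5 × −0.798 + 0.3 × 0.798)/0.8 = −0.20 SD, a spurious VR advantage. In simulation with 20 per arm the type I error was about 8% (bias −0.19 SD).
- *Same half-selection in both arms:* simulated bias about zero, type I error about 4%.
- *Logistic dropout, slope 1 per SD of the Post-test 1 score:* 0.12 to 0.28 SD at about 13% to 33% loss if improved women leave VR-first and unimproved women leave TAU-first. It is 0.06 to 0.14 SD if selective loss occurs in VR-first only. If the score drives loss in the same way in both sequences, it is zero with no true effect and 0.02 to 0.04 SD with a true effect of 0.5 SD.

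Reversing the pattern reverses the sign.

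**5. The alternative.** Suppose loss is confined to Post-test 2, the means are free for each sequence and time, and the covariance is unstructured. The generalised least-squares means at Pre and Post-test 1 then equal the simple means over all women in the sequence. A numerical check confirmed this. The first-period estimate therefore uses all 40 women and does not depend on who returns for Post-test 2.

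**The case against.** The strongest reply is that the article nowhere says that women without Post-test 2 are excluded. The words in brackets, Mixed Model, could mean a linear mixed model fitted by likelihood, which keeps such women, and the fix would then already be in place. The article also separates the two intervals itself, and nothing restricts the first to three-visit completers. The sample-size paragraph names no test family, so it cannot settle the matter.

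Most of this stands. A reader might infer that the plan prescribes deletion; the text does not support that. What remains is that the analysis is called an ANOVA and is described by factor levels, which is how a mixed-design ANOVA is normally written, and that form deletes partial cases by default.

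A reader might also infer that dropout will differ by sequence. The documents show only that it could: the second treatments differ, but no dropout rate or pattern is given. One can build a case of 0.40 SD by letting the least improved leave one arm and the most improved leave the other. That result comes entirely from the assumption and should not be the headline.

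Finally, a reader might fault the article for having no missing-data rule or no plan to follow women who stop sessions. Condensed articles commonly leave such matters to the full protocol or SAP, so neither is raised here.

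**Conclusion.** The concern holds in conditional form. On its ordinary reading, the stated model makes the randomised VR-versus-TAU comparison depend on completing an assessment that the comparison does not need. The wording should rule this out.

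The loss of precision follows from any second-period dropout under that reading: at an assumed 20%, about 12% on the standard error and about 9 percentage points of power. Bias is possible but not shown. It needs leaving to depend on first-period response differently by sequence, and under the patterns above it is about 0.06 to 0.28 SD in either direction. All sizes rest on the assumed dropout, ρ = 0.5, 1:1 allocation and a complete Post-test 1.

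This is an improvement available at almost no cost, not an error that invalidates the design. If a likelihood-based model was meant all along, only the wording changes.

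**What to change.** In the analysis paragraph, replace the ambiguous label by one of two statements.

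- **Preferred:** a likelihood-based linear mixed model (REML) with categorical time, sequence and their interaction, unstructured covariance and small-sample degrees of freedom such as Kenward-Roger. It includes every randomised woman in her assigned sequence with every assessment she provided. The Pre to Post-test 1 contrast between sequences is named as the test of hypothesis (a).
- **Alternative:** test hypothesis (a) separately by ANCOVA of Post-test 1 adjusted for the Pre score, in all randomised women with Post-test 1. Keep the three-time model for the later interval.

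Either way, say explicitly that a missing Post-test 2 does not remove a woman from the first-period comparison. The cost is a sentence or two of text and slightly more analysis work, with no additional participants, visits or questionnaires.

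### Treating Pre as a level of Time makes VR versus TAU a change-score comparison: valid, but less efficient than adjusting for Pre (about 6 to 10 power points if the pre/post correlation is 0.5)

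*Protocol article*

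**What the plan says.** The analysis is set out in the last paragraph under Satisfaction With the Intervention, within Measures and Data Analysis: "we will perform repeated measures (Mixed Model) ANOVA with 3 Times (Pre, Post-test 1, Post-test 2) and 2 Conditions". The two conditions are the two treatment orders, VR first or TAU first. The same paragraph says where the main comparison comes from: "The Pretest to Post-test 1 allows the comparison of VR-based treatment versus TAU". Post-test 1 to Post-test 2 is kept for the added value of VR after TAU. Hypothesis (a), at the end of the Introduction, is a greater symptom reduction with VR given first than with TAU.

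The article nowhere makes the Pre score a covariate or constrains the Pre means to be equal in the two conditions.

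Under Inclusion/Exclusion Criteria: "The target sample will be composed of 40 women". The calculation uses f = 0.25, at least 90% power and "a significance level of 0.05". It gives no pre/post correlation and does not say which effect f refers to. Under Procedure: "Women will be randomly assigned to the VR+TAU or to the TAU + VR condition". Randomisation is unstratified and no allocation ratio is given.

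**The concern.** When Pre is an outcome level, the Pre to Post-test 1 by Condition contrast subtracts each woman's whole Pre score from her Post-test 1 score. That fixes the slope on Pre at 1. With equal variances the slope that best predicts Post-test 1 is the pre/post correlation, which is below 1, so the change score removes too much of a chance Pre difference and carries avoidable noise. The model also leaves unused the fact that randomisation makes the Pre means equal in expectation.

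What is at stake is precision. The trial has 40 women and already collects the Pre scores, so power lost here could be recovered without recruiting anyone.

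**Working it through.** **The plan's own figure.** For a repeated-measures interaction with m times, I used lambda = N x m x f^2 / (1 - rho), with m - 1 and (N - 2)(m - 1) df and sphericity. With N = 40, f = 0.25 and rho = 0.5:
- Three times: lambda = 40 x 3 x 0.0625 / 0.5 = 15, power 93.5%.
- Two times: lambda = 10, power 86.9%.

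The 40 meets the 90% target under the three-time reading. Because the correlation and the test are not stated, the figure can be neither confirmed nor shown wrong.

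**Inputs for the comparison.**
- From the article: 40 women, alpha 0.05.
- Assumed: two-sided test, 20 per arm, no dropout, equal Pre and Post variances.
- Assumed, shown as a range: correlation rho from 0.3 to 0.8.
- Assumed, shown as a range: true VR-TAU gap at Post-test 1 of 0.5 to 1.0 SD. The gap is 0.5 SD if f is half the standardised difference, and 1.0 SD if f = 0.25 is a 2 x 2 interaction (4 x 0.25).

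**Variances, in units of SD squared.**
- Change score: 2(1 - rho), with 38 df for a plain t test or 76 df with the ANOVA's pooled error.
- ANCOVA: (1 - rho^2) x (1 + 1/36), with 37 df. The factor 1 + 1/36 is the small-sample cost of estimating the slope.

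Apart from that factor, the ratio of ANCOVA to change-score variance is (1 + rho)/2. At rho = 0.5 it is 0.75, so the change score needs 1/0.75 = 1.33 times as many women for the same precision.

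**One case in full (rho 0.5, gap 0.8 SD).**
- Change score: variance 1.00, SE = sqrt(2 x 1.00/20) = 0.316, non-centrality 0.8/0.316 = 2.53. Power is 69.3% (38 df) or 70.5% (76 df).
- ANCOVA: variance 0.75 x 1.028 = 0.771, SE = sqrt(2 x 0.771/20) = 0.278, non-centrality 2.88. Power is 80.1%.

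**Non-central t power (%).** Losses were taken before rounding.

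| rho | gap (SD) | change t test, 38 df | planned contrast, 76 df | ANCOVA | loss of planned contrast (points) |
|---|---|---|---|---|---|
| 0.3 | 0.5 | 25.6 | 26.1 | 35.7 | 9.5 |
| 0.3 | 0.8 | 54.9 | 56.0 | 72.2 | 16.2 |
| 0.3 | 1.0 | 74.0 | 75.1 | 89.0 | 13.8 |
| 0.5 | 0.5 | 33.8 | 34.5 | 41.9 | 7.3 |
| 0.5 | 0.8 | 69.3 | 70.5 | 80.1 | 9.7 |
| 0.5 | 1.0 | 86.9 | 87.7 | 93.9 | 6.2 |
| 0.7 | 0.5 | 51.2 | 52.2 | 56.6 | 4.4 |
| 0.7 | 0.8 | 88.9 | 89.7 | 92.5 | 2.8 |
| 0.7 | 1.0 | 97.8 | 98.1 | 98.9 | 0.8 |
| 0.8 | 0.5 | 68.3 | 69.4 | 71.6 | 2.2 |
| 0.8 | 0.8 | 97.4 | 97.7 | 98.2 | 0.5 |
| 0.8 | 1.0 | 99.8 | 99.9 | 99.9 | 0.0 |

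Against the plain change-score t test at rho 0.5, the loss is 8.1 points at 0.5 SD and 10.8 at 0.8 SD. Simulation with 20,000 trials per setting gave 8.1 and 11.1.

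**Against the 2-df Time x Condition test.** Let the gaps at the three times be 0, d, and then either 0 or d. Both patterns give lambda = (20/2) x (2/3)d^2 / (1 - rho), with 2 and 76 df. At rho 0.5 its power is 34.1%, 72.9% and 90.4% for d = 0.5, 0.8 and 1.0 SD, so ANCOVA gains 7.8, 7.2 and 3.5 points. At rho 0.7 the gains are 3.4, 0.4 and about 0.

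**The case against.** The strongest reply is that nothing here is an error. The planned ANOVA keeps its type I error, its estimate is unbiased under randomisation, and change from Pre matches a hypothesis worded as a reduction in symptoms. That stands. A reader might infer from the imbalance argument that the result will be biased, but the article does not support this. With 20 per arm the chance Pre difference has SD sqrt(2/20) = 0.32 SD and exceeds 0.3 SD in about 34% of randomisations. Those differences are already counted in the change-score variance, so they explain the power loss and are not a second defect.

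The size also rests on inputs outside the article. Assessments are 3 weeks apart and one measure is trait anxiety, so correlations above 0.5 are plausible for some outcomes, and the gain fades there. The omnibus test is closer to ANCOVA at the larger gaps, although it mixes in Post-test 2, whereas the article ties VR versus TAU to Pretest to Post-test 1. This limits the size but does not remove the point.

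Unequal variances matter as well. If Post SD is 1.2 times Pre SD, the gap is 0.5 Pre SD and rho is 0.8, ANCOVA is slightly behind a plain change-score t test (56.0% against 57.0%). That reversal comes only from the small-sample factor. In large samples, in units of the Pre variance, the change score's excess variance is (1 - rho x SDpost/SDpre)^2, which is never negative.

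Finally, an analysis plan that is not shown might add covariates. But the article does not leave the model open: it names the factor, its levels and the contrast.

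**Conclusion.** The point holds as a matter of efficiency. As written, VR versus TAU is tested on change scores, although the Pre score is available as a covariate at almost no cost. With 20 per arm, equal variances and a correlation of 0.5, the planned contrast gives up about 6 to 10 power points for gaps of 0.5 to 1.0 SD. The loss is about 9 to 16 points at 0.3, about 1 to 4 at 0.7 and about 0 to 2 at 0.8. Against the omnibus test it is about the same at a gap of 0.5 SD and smaller at larger gaps.

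Two stronger readings are not supported. A loss of 8 to 11 points is not a property of the trial: it belongs to a plain change-score t test at an assumed correlation of 0.5 and gaps of 0.5 to 0.8 SD. Nor does the comparison show that 40 women is wrong, since that number reaches its stated power under one ordinary reading of the calculation.

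**What to change.** For hypothesis (a), state that Post-test 1 is compared between conditions by ANCOVA with the same outcome's Pre score as covariate. If the longitudinal model is kept, either take Pre out of the Time factor and enter Pre and Pre x Time as covariates, or keep Pre as an outcome and constrain its mean to be equal in the two conditions.

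Apply this to every outcome with a true baseline score. CGI improvement and treatment response are excluded: each is rated relative to treatment and has no genuine Pre value.

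For any between-condition comparison at Post-test 2, adjust for Pre and not for Post-test 1, which treatment has already affected.

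The cost is one sentence and, for the ANCOVA, one residual degree of freedom. No new women, visits or data are needed.
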